#### *O'Brien Fleming Boundary for a Binary Primary Endpoint*

*For a RCT comparing two treatment arms with respect to a binary outcome and one interim analysis, the binary test statistic is given as*

$$Z_k = \frac{(p_{Ak} - p_{Bk})}{\left\{ \sqrt{\bar{p}_k(1 - \bar{p}_k) / \left( \frac{1}{n_A} + \frac{1}{n_B} \right)} \right\}}, k = 1, \dots, K = 2$$

where  $\bar{p}_k = \frac{p_{Ak} + p_{Bk}}{2}$ , where  $P_{Ak}$  and  $P_{Bk}$  are the estimated proportions in treatment arms A and B at stage k, respectively. The two-sided sequential test based on O'Brien & Fleming boundary is given as

1. At stage 1 (interim analysis, n=300): Reject  $H_0$  and stop the trial at stage k if:  
 $|Z_k| \geq C_B(2_{z0.05})\sqrt{2} = 2.834$

Else if  $|Z_k| < C_B(2_z 0.05)\sqrt{2} = 2.834$ , continue to stage 2.

2. At stage 2 (final analysis): Reject  $H_0$  at stage  $k$  if:  $|Z_k| \geq C_B(2_z 0.05) = 2.004$

Therefore, for a RCT with one interim analysis and a final analysis (i.e.,  $K = 2$ ), the critical boundaries at Stage 1 and Stage 2 (final analyses) are 2.834 and 2.004, respectively.

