#### 4. Interim Analyses

We will plan for two interim analyses after 125 and 300 patients have completed 3-month follow-up. At the safety analyses (n=125) the DSMB will be asked to consider safety only. The second analysis (n=300) will assess for safety and overwhelming efficacy and make recommendations accordingly. We will use O'Brien-Fleming boundaries at the interim analysis as follows:

There are no established techniques for the assessment of interim trial efficacy boundaries using an ordinal logistic regression model (proportional odds model). Instead, we will revert to a simple dichotomous analysis of the mRS score at 0-2 defined at 90 days from randomization. [This approach is also being used in other interventional treatment trials in stroke.] The Z-statistic for this analysis shall be derived from the normal approximation of the binomial distribution as an unadjusted two-sample test of proportions.

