### **Instructions to DSMB: Stopping Rules/Guidance**

- Thus, if the Z statistic is greater than 2.834 at the interim analysis, the committee will then consider that there is statistical evidence for overwhelming efficacy.
- The committee should then consider the primary outcome analysis using the ordinal logistic regression (proportional odds model).
- Next the committee should consider any effect upon all-cause mortality
- Finally the committee should consider the treatment effect in two subgroups: patients treated with IV tPA and patients not treated with IV tPA.

**The committee is then entrusted with a decision to make recommendations about the continuation of the trial in the context of the data and the context of the current and known evidence about endovascular stroke treatment using their best judgment.**

Because of past experience with IMS-3 and published results from the Penumbra, SWIFT and TREVO trials, we have confidence in the safety of endovascular treatment. However, as has evolved in past trials of hemicraniectomy in stroke, and in the SWIFT trial, there is a possibility that mortality in the control group may be higher than the treatment group, even when a morbidity benefit is not evident. Because our objective is to demonstrate a morbidity benefit, the DSMB will be asked to consider such a result (mortality benefit) carefully before recommending that the trial continue or be halted. This will be facilitated by having stringent futility and overwhelming efficacy boundaries using O'Brien-Fleming methods (which are known to be conservative at the interim analysis stage). There will be no analysis for futility.

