## 6. Randomization

Randomization will be managed using a custom SQL server-based database that will instantly and dynamically assign treatment using the minimal sufficient balance algorithm. Randomization will therefore be conducted over the internet via a desktop computer or a web-enabled smart phone.

Randomization will be 1:1. Allocation will be 1:1 set at  $p(0.5)$  for the first 40 patients. Thereafter, a minimization algorithm (minimal sufficient balance) will be utilized to ensure ongoing balance in the trial on the following factors:

- Age

- Baseline NIHSS score

- Sex (male or female)

- Baseline ASPECTS score, dichotomized as 6-7 or 8-10.

- Intracranial occlusion location, dichotomized as MCA or ICA.

- IV tPA use (yes or no)

The minimal sufficient balance (MSB) randomization is a minimization procedure that preserves balance in smaller trials, such as this one, where imbalances in important baseline prognostic variables may occur by chance and confound the primary outcome. In addition, it preserves a greater degree of randomness in patient allocation compared to permuted block designs. Because of the MSB process, randomization assignments will be stochastically derived in real time using a interactive web-site and therefore concealment can never be breached. Allocation will be open.

Reliance on a process that requires real-time data entry makes the process susceptible to error. For example, incorrect information (eg. wrong sex or incorrect site of occlusion) could be mistakenly entered into the randomization process and affect the minimization algorithm. Post-hoc, when such errors become known, the quality-controlled database entry will be considered the source of truth and the randomization database will be updated to ensure that ongoing randomization utilizes the most correct data to determine balance in an ongoing way.

The randomization process is not blocked, nor stratified by site. Therefore, the number of patients enrolled into each arm of the study may not be exactly even at the time the study is completed. The proportion of patients enrolled into each arm at each site may also vary and not be equally distributed. These decisions were taken explicitly with the knowledge and belief that balance on 6 key patient characteristics in the trial overall are more important than balance by site.

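### The printed interim Z formula divides by (1/nA + 1/nB) where the test named in the same section multiplies; coded as printed, Z could not reach the 2.834 trigger at n=300

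*SAP*

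**What the plan says.** Section 4 plans one look for efficacy: "The second analysis (n=300) will assess for safety and overwhelming efficacy". Because the authors see no established boundary method for the ordinal model, they turn at that look to "a simple dichotomous analysis of the mRS score at 0-2 defined at 90 days from randomization". In words, the Z statistic is "derived from the normal approximation of the binomial distribution as an unadjusted two-sample test of proportions".

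The subsection on the O'Brien-Fleming boundary then gives a formula, introduced by "with respect to a binary outcome and one interim analysis, the binary test statistic is given as". Its numerator is pAk − pBk. Its denominator is the square root of pbar(1 − pbar) divided by (1/nA + 1/nB), with an explicit slash. There pbar is half the sum of the two arm proportions.

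The subsection concludes that "the critical boundaries at Stage 1 and Stage 2 (final analyses) are 2.834 and 2.004, respectively". The instructions to the DSMB use the first of these values as the trigger: the committee is to regard overwhelming efficacy as statistically supported "if the Z statistic is greater than 2.834 at the interim analysis", and then goes on to the ordinal model, mortality and the IV tPA subgroups.

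On arm sizes, Section 6 says "Randomization will be 1:1" but also that "the number of patients enrolled into each arm of the study may not be exactly even".

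**The concern.** The verbal description and the formula define different statistics. The variance of a difference between two independent proportions falls as the arms grow, because it is proportional to (1/nA + 1/nB). In the printed form that term sits in the wrong place, so the denominator grows with sample size and the same observed difference gives a smaller Z when more patients are followed. Such a quantity does not have unit variance under the null hypothesis and cannot be compared with a normal-theory boundary.

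This formula is the only one given for the statistic behind the trial's only formal efficacy threshold. A programmer who coded the line as printed, or validated a program against it, would produce a rule that never signals benefit.

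**Working it through.** **Inputs.** The efficacy look is at n=300 (Section 4). Allocation is 1:1 (Section 6), so 150 per arm is taken as the working split. The boundaries are 2.834 and 2.004 (Section 4). The readable text gives no rates of mRS 0-2, so every rate below is an assumption, and a range is shown.

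**The plan's own figures.** 2.004 × √2 = 2.834, so the two stated boundaries agree with each other. The SAP gives no worked value of Z to reproduce. The boundaries are taken as given here.

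**The two forms.** Write d = pA − pB, v = pbar(1 − pbar) and s = 1/nA + 1/nB.

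- Test named in words: Z = d / √(v × s)
- Formula as printed: Z = d / √(v / s)
- Ratio of the first to the second: 1/s

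At 150 per arm, s = 2/150 = 1/75, so the printed Z is the correct Z divided by 75. At 140 and 160 the factor is 74.7.

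**Largest value the printed form can take.** For a given pbar of at most 0.5, d cannot exceed 2 × pbar, so d/√v is at most 2√(pbar/(1 − pbar)). This rises to 2 at pbar = 0.5, the case of 100% against 0%; values of pbar above 0.5 mirror it. The printed |Z| is therefore at most 2√s.

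- At 150 per arm: 2 × √(1/75) = 0.231. Evaluating every possible pair of counts at 150 per arm gives the same maximum.
- Over every split of 300 patients, the maximum comes at the absurd split of 1 and 299: 2 × √(1 + 1/299) = 2.003, still below 2.834.

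The impossibility therefore needs no assumption about event rates and does not depend on equal arms.

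**Illustrations at 150 per arm (assumed rates of mRS 0-2).**

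| Rates | Correct Z | Printed Z | Correct Z reaches 2.834? |
|---|---|---|---|
| 45% vs 35% | 1.77 | 0.024 | no |
| 50% vs 35% | 2.63 | 0.035 | no |
| 55% vs 35% | 3.48 | 0.046 | yes |
| 60% vs 30% | 5.22 | 0.070 | yes |

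For 55% vs 35%: pbar = 0.45 and v = 0.2475. The correct form is 0.20/√(0.2475/75) = 0.20/0.0574 = 3.48. The printed form is 0.20/√(0.2475 × 75) = 0.20/4.308 = 0.046.

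The slip changes the reading of the rule only where the correct Z would reach 2.834. At 150 per arm that takes an observed difference of about 15 to 17 percentage points for control rates from 20% to 40%.

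**The definition of pbar.** The simple mean equals the pooled proportion only when the arms are equal. At 140 with 55% and 160 with 35%, the simple mean is 0.450 and the pooled proportion is (77 + 56)/300 = 0.443. With the multiplying form, Z is 3.474 with the first and 3.479 with the second, a change of about 0.1%.

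**The case against.** The strongest reply is that Section 4 already names the right test in words. Any standard routine for two proportions gives the correct Z, and a statistician who saw a value such as 0.05 for a 20-point difference would find the slip at once. This stands. It means that the consequence is conditional on someone coding the printed line. It does not remove the conflict, because one section should not define its decision statistic in two incompatible ways.

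A second reply is that equations can be damaged when text is taken from a PDF, and other notation in this subsection looks garbled. That is a reason to check the original. A lost character is an unlikely explanation, however, because the correct formula has no slash at that point. Division would be right only if the divisor were the reciprocal of the printed term, nA × nB/(nA + nB).

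Third, the DSMB text is guidance. Crossing 2.834 opens a sequence of considerations that ends in the committee's judgment, so the threshold does not stop the trial by itself. This also stands, but the threshold is still the stated entry to that sequence.

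A reader might go further and infer that the final analysis could never succeed, because the subsection also sets 2.004 for a second stage and the printed form peaks at 0.20 with 200 per arm. The SAP does not support that. Section 9.1 makes the primary analysis an unadjusted proportional odds model, with Fisher's exact test on mRS 0-2 as the fallback, and neither uses this formula. A reader might also infer that an interim result was miscalculated. Nothing in the document shows how the interim was programmed.

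**Conclusion.** The printed Z formula is wrong as it stands and contradicts the test that Section 4 names. Used literally at n=300 with 150 per arm, it makes Z 75 times too small, with a ceiling of 0.231 against a trigger of 2.834. This rests on the slash being present in the original PDF; the factor of 75 also rests on an even split, while the failure to reach 2.834 holds for every split.

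The effect is limited to the interim efficacy rule, and to the case where the printed line is followed instead of the named test. It does not touch the primary final analysis. The definition of pbar is a minor imprecision with a negligible effect at plausible imbalances.

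**What to change.** Check the sign in the original PDF. If the slash is there, replace the line with:

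Z_k = (pAk − pBk) / √{ pbar_k (1 − pbar_k) (1/nAk + 1/nBk) }

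In the same line, as a tidy-up, define pbar_k as total successes over total patients at look k, (xAk + xBk)/(nAk + nBk), since Section 6 allows the arms to differ. Then confirm that any program used for the interim analysis computes this form. One test case is enough: 55% vs 35% at 150 per arm must return 3.48.

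The cost is one line of the SAP and a short program check. Sample size, boundaries and the final analysis are unchanged.

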### 3. Sample size

There is now empirical evidence that the mRS scale, when categories 5 and 6 are combined, is a truly interval scale meaning that the difference in utility (or function) between any one step increment in the scale is the same; thus, it is unlikely that the proportional odds assumption will be violated. The trial is powered to detect a statistically significant shift in the distribution of scores on the mRS scale at 3 months between the treatment and the control arm, assuming that categories 5 and 6 (bedbound with severe disability, and death) are collapsed into one category, and the effect leads to an assumed common odds ratio of 1.8. The expected distribution of outcomes is based upon the pooled experience from the literature [SWIFT study, STAR registry, Calgary data, IMS-3 study limited to an ESCAPE population, ALIAS part 1 study limited to an ESCAPE population] and a 5% increase in favourable outcome per mRS category. [Figure 1] In IMS-3 there was an average 2% non-significant improvement in favourable outcomes per mRS category; in SWIFT (which compared two endovascular devices), there was an average 8% improvement in favourable outcomes per mRS category. Using Calgary data, the common OR for improvement across the mRS scale with endovascular treatment compared to IV only was 2.1 (CT95 1.1-4.2). [[name], unpublished data]

A total sample size of 188 patients per group is required for 90% power, two-sided alpha at 0.05 and 1:1 randomization to detect a common OR of 1.8, based upon the expected distribution shown below (figure 1). The sample size calculation is based upon Whitehead's power formula. The sample size is estimated without knowing the distribution of pre-specified confounding variables. We assume no cross-overs. Allowing for losses-to-follow-up (of up to 6%, n=24/400), a total required sample size of 400 ideal patients is anticipated. However, we know that the effect size is highly dependent upon very rapid treatment times and have planned to continue enrolling patients until up to 200 endovascular patients have been treated with a CT-to-first reperfusion time < 90 minutes. Currently, in our initial patients we are meeting this quality metric in 60% of our patient population, compared to our desired 80% or greater. We conservatively assume that the effect size is absent if we do not achieve our target treatment times. Therefore,

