(1) the trial is powered to detect an effect size based upon 400 ideal patients

(2) the maximum sample size for the trial will be 500 patients to ensure that 200 patients in the endovascular group meet the target treatment times (i.e. are ideal patients).

Figure 1. Projected outcomes by mRS category

[figure not shown]

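### The O'Brien-Fleming pair 2.834 / 2.004 joins the three-look constant to a half-information factor, so the n=300 efficacy bar is stricter than the named method sets

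*SAP*

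**What the plan says.** Section 4 announces the looks: "We will plan for two interim analyses after 125 and 300 patients have completed 3-month follow-up". The first is not an efficacy look: "At the safety analyses (n=125) the DSMB will be asked to consider safety only". The second is: "The second analysis (n=300) will assess for safety and overwhelming efficacy". The boundary family is named: "We will use O'Brien-Fleming boundaries at the interim analysis as follows".

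The subsection on the binary endpoint describes a trial "with respect to a binary outcome and one interim analysis", sets K = 2, and labels its constant as the one for two looks at 0.05. It gives that constant as 2.004, multiplies it by √2 for the interim, and concludes that "the critical boundaries at Stage 1 and Stage 2 (final analyses) are 2.834 and 2.004, respectively". The instructions to the DSMB repeat 2.834 as the trigger.

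Section 3 supplies the error rate ("two-sided alpha at 0.05 and 1:1 randomization") and the sample size. It says that "the trial is powered to detect an effect size based upon 400 ideal patients" and allows enrolment to rise to at most 500, so that 200 endovascular patients meet the treatment-time target. Neither section gives an alpha-spending function or a rule for adapting the boundary to the final N.

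**The concern.** Two things do not fit the stated design.

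- **The constant.** The value 2.004 is not the two-sided 5% O'Brien-Fleming constant for two looks.
- **The multiplier.** The factor √2 is 1/√t at t = 0.50. The planned look falls at t = 0.60 to 0.75.

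The interim value is what the DSMB compares Z with before it regards efficacy as statistically overwhelming and goes on to the ordinal result, mortality and the tPA subgroups. If it is higher than the named method requires, a benefit that would pass a correctly timed O'Brien-Fleming boundary can miss the trigger. Up to 100 (N=400) or 200 (N=500) further patients would then be randomized. The values are also presented as the standard 5% boundary, so a reader would not know that they are stricter.

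**Working it through.** **Inputs (SAP sections 3 and 4).** Two-sided alpha 0.05; two efficacy looks; interim at 300; final N of 400 to 500; stated pair 2.834 / 2.004.

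**Step 1: reproduce the plan's figures.** 2.004 × √2 = 2.834, so the interim value is the stated constant times √2. To find where 2.004 comes from, solve for C with boundaries C/√t_k, correlation √(t_j/t_k) between looks j < k, and total two-sided error 0.05:

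| Equally spaced looks | C | Boundaries |
|---|---|---|
| K = 2 | 1.977 | 2.797 / 1.977 |
| K = 3 | 2.004 | 3.471 / 2.454 / 2.004 |
| K = 4 | 2.024 | 4.049 / 2.863 / 2.337 / 2.024 |

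The stated constant is that of K = 3. Counting the n=125 look does not recover the pair: looks at 125/300/500 give 3.985 / 2.572 / 1.992, and looks at 125/300/400 give 3.607 / 2.328 / 2.016.

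**Step 2: timing.** 300/500 = 0.60 and 300/400 = 0.75. The classical shape solved at these fractions, and the error of the stated pair, are:

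| t | O'Brien-Fleming shape | Two-sided alpha of 2.834 / 2.004 |
|---|---|---|
| 0.50 | 2.797 / 1.977 | 4.69% |
| 0.60 (N=500) | 2.572 / 1.992 | 4.63% |
| 0.75 (N=400) | 2.327 / 2.015 | 4.55% |

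The alpha is 1 − P(|Z1| < 2.834 and |Z2| < 2.004) with correlation √t.

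**Step 3: chance of crossing at n=300.** Assume 150 per arm, an odds ratio of 1.8 on mRS 0-2 in every patient, and a control rate p of 20% to 43%. The SAP gives no such rate in readable form, because Figure 1 is not shown. The mean of Z is (q − p) / √[p̄(1 − p̄) × 2/150], where q is the treated rate and p̄ the average of p and q.

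- p = 0.20: odds 0.25 × 1.8 = 0.45, q = 0.310, p̄ = 0.255, mean Z = 0.1103/0.0503 = 2.19.
- p = 0.43: odds 0.754 × 1.8 = 1.358, q = 0.576, p̄ = 0.503, mean Z = 0.1459/0.0577 = 2.53.

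The chance of crossing c is about 1 − Φ(c − mean Z):

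| Interim value | p = 0.20 | p = 0.43 |
|---|---|---|
| 2.834 (stated) | 26% | 38% |
| 2.572 (N=500) | 35% | 48% |
| 2.327 (N=400) | 45% | 58% |

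Correcting only the constant (2.834 to 2.797) moves the chance little: from 36.7% to 38.1% at p = 0.35. Most of the gap comes from timing.

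**Step 4: overall power.** If a fixed-sample test of mRS 0-2 had 90% power (an assumption; the SAP gives that power for the ordinal endpoint), the stated pair has 89.3% against 89.6% for the correctly timed rule at t = 0.60, and 89.2% against 89.5% at t = 0.75.

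**Step 5: spending-function values.** At 2.5% per side, the O'Brien-Fleming-type function spends 2[1 − Φ(2.2414/√t)] per side, where 2.2414 is the normal quantile for an upper tail of 0.0125.

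- t = 0.60: 2[1 − Φ(2.894)] = 0.0038 per side, giving 2.669, then 1.981 at the final.
- t = 0.75: 2[1 − Φ(2.588)] = 0.0096 per side, giving 2.340, then 2.012.

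The function applied once to the whole two-sided 5% gives 2.530 / 1.999 and 2.263 / 2.037 instead, so the convention must be named.

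**The case against.** The strongest reply is that the error is safe. Alpha stays below 5%, overall power falls by a fraction of a point, and the SAP says that it wants stringent boundaries and a finding of overwhelming efficacy. That stands as to severity. It does not make the figures right: the SAP presents them as the O'Brien-Fleming values for two looks and does not declare a stricter choice.

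Three further replies carry weight.

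- **The final value is close.** 2.004 lies between the timing-correct finals of 1.992 and 2.015, so it is not materially wrong in itself. Those finals do, however, belong with much lower interim values. If 2.834 were kept at the interim, the final value need only be 1.970 (t = 0.60) or 1.963 (t = 0.75).
- **The DSMB keeps its judgment.** Crossing 2.834 is a trigger and not an automatic stop. But the guidance begins from that crossing, so the number still matters.
- **The crossing probabilities are assumption-bound.** They apply the full effect to all 300 patients, whereas section 3 assumes no effect where the treatment-time target is missed and reports it met in 60% so far. Real chances would be lower at every boundary.

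A reader might infer that the trial's false-positive risk is inflated, or that this pair is the sole formal criterion for the trial. The SAP supports neither. The error runs the other way, and section 9.1 makes an unadjusted proportional odds model the primary analysis, while the pair is written for the binary Z. The 4.55-4.69% figures therefore describe the binary two-stage rule and not the primary ordinal test.

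**Conclusion.** The point holds as an error of constant and timing in a stated decision threshold. The pair 2.834 / 2.004 is not the 5% O'Brien-Fleming boundary for two looks at equal spacing, nor at the planned timing.

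The consequence is confined mainly to the interim. Relative to the correctly timed O'Brien-Fleming shape, the chance of crossing at n=300 is lower by about 9-10 percentage points if N is 500 (26-38% against 35-48%) and by about 19-20 points if N is 400 (26-38% against 45-58%). This rests on an odds ratio of 1.8 in all patients and an assumed control rate of 20-43%. The boundary values and alpha figures rest only on the stated alpha, the number of looks and the 300/400/500 patient counts, taking information as proportional to patients.

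This should be fixed before the n=300 look. It does not threaten validity.

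**What to change.** In the boundary subsection of section 4 and in the DSMB instructions:

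1. Replace the fixed pair with a Lan-DeMets O'Brien-Fleming-type spending function at 2.5% per side, and name that convention.
2. State in advance the N that defines the interim information fraction. With the 500 maximum (t = 0.60) the values are 2.669 / 1.981; with 400 (t = 0.75) they are 2.340 / 2.012.
3. Recompute the final critical value from the alpha left, at the N actually reached. For example, if the interim used 2.669 and the trial ended at 400, the integral of step 2 with correlation √0.75 gives a final value of 1.969.
4. State that this final value applies to the binary Z, and say what critical level the primary ordinal test in section 9.1 uses.

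Merely substituting the two-look constants (2.797 / 1.977) would correct the look-up error but leave the timing error: 2.797 is still above 2.572 and 2.327, and 1.977 is further from the timing-correct finals than 2.004 is.

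The cost is a paragraph in the SAP, matching DSMB wording and a few lines of code.
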